#### Quantitative data analysis

##### Preliminary and descriptive analyses

All data will first be assessed for missingness and out-of-range values with basic statistical procedures such as univariate statistics (means, standard deviations, ranges, frequencies, proportions, percentiles) and graphs such as histograms, box and whisker plots, scatter plots and Q-Q plots. In addition, plots may be produced of individual and average trajectories of all repeated measures over time according to assigned treatment. All questions of data quality and integrity will be investigated before any statistical modeling, as complete and accurate data are essential for unbiased estimates and confidence intervals. Baseline and demographic characteristics will be summarized overall for all participants and by intervention group. Univariate summary statistics will be provided for continuous variables and frequencies for categorical variables. Graphical methods mentioned above will be used to examine distributions and identify potential influential points. Assumptions of all statistical models for the aims will be assessed; data transformations for variables may be considered in analyses if required to meet assumptions of the statistical tests/models. Missing data will be assessed, and sensitivity analyses will be considered. Scale data where participants answered at least 80% of the items will be imputed using person-mean substitution. In instances where a participant omits more than 80% of the items from a specific scale, responses from that scale will be excluded from analysis.

###### Aim 1

To assess the feasibility and acceptability of PJB, we will use routinely collected data on study engagement among potential participants and 12-month endline survey data among PJB participants. Quantitative data analysis: Feasibility: We will assess the number and proportion of participants reached by PJB by creating quarterly reports from the routine data. We will compile absolute numbers for the following: (1) # who indicate interest; (2) # invited to enroll; (3) # who enroll; (4) # who are referred for care services. Acceptability: We will describe perceived acceptability quantitatively using 11 items on spending and decision-making control and ten items about the timing of GI payments from the endline survey. Acceptability of each care service will be evaluated using six items from the endline survey and acceptability of PJB and its evaluation will be assessed using three survey items. Qualitative data analysis: We will also examine perceived acceptability in the participatory session and will analyze data following procedures in Aim 2.

###### Aim 2

Examine *whether* and *how* a guaranteed income affects parental stress, ability to meet basic needs, engagement in healthcare and bandwidth for parenting among recipients of the cash + care. Quantitative data analysis: we will use survey data to examine *whether* receiving cash + care affects outcomes using two steps. First, we will describe baseline demographic characteristics among those who receive cash + care. Second, we will examine differences in parental stress, basic needs, engagement in care and bandwidth for parenting over follow-up (baseline, 6 months postpartum, and 12 months postpartum surveys). We will use mixed effects regression models with a fixed effect for time (categorical) and random participant-level intercepts. We will examine the sensitivity of our findings to the inclusion of key potential confounders in the model, including SES and pregnancy-related variables (e.g., gravidity, parity, maternal health conditions). Using these models, we will estimate and report the average difference in outcome between groups over follow-up with 95% confidence intervals. We will also characterize outcome patterns over time by presenting estimated mean outcomes at each time point individually.

###### Aim 3

Explore the preliminary impact of PJB on parental mental health and prematurity. The purpose of the PJB is to reduce disparities in birth outcomes. Given the limited numbers of participants in this pilot program and evaluation study, however, we are underpowered to examine such disparities. Consequently, birth outcomes are included as exploratory analysis for potential signals of GI impact. Another important outcome for the PJB evaluation study is perinatal depression, which we do have sufficient statistical power to examine. Perinatal depression is also associated with adverse birth outcomes and can be a marker for perinatal health.

To investigate post-baseline differences in continuous EPDS depression score in the cash + care and care groups, our primary analyses will use mixed effects regression models with fixed effects for time (baseline, 6 months postpartum and 12 months postpartum), group, and the interaction between time and group and random participant-level intercepts. Using these models, we will estimate and report the average difference in depression score between groups over follow-up with 95% confidence intervals. We will also characterize outcome patterns over time by presenting estimated mean outcomes at each time point individually. We will use the same approach to examine post-intervention differences anxiety score. In secondary analyses, we will examine differences in infant birthweight and preterm birth in the cash + care vs. care groups using logistic regression. Birthweight and gestational age at birth will be determined using data from birth records and classified as low birthweight <2,500 grams (y/n) and preterm birth <37 weeks (y/n). We will examine the sensitivity of our findings to the inclusion of key potential confounders in our models, including SES and pregnancy-related variables (e.g., gravidity, parity, maternal health conditions).

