#### Outcomes

Low birth weight will be extracted from the birth record and defined as an absolute weight of <2,500 g regardless of gestational age (27). Preterm birth will be extracted from the birth record and defined as birth prior to 37 weeks gestation (27).

Depression will be assessed using the Edinburgh Postnatal Depression Scale (EPDS), a measure validated for use during and up to 24 months after pregnancy (28–31). The scale consists of 10 items scored on a 4-point Likert scale which ask about common depressive symptoms experienced in the prior week. We will characterize this primary outcome using a continuous score because subclinical symptoms can impact functioning (32, 33). Additionally, we will characterize probable depression (yes vs. no) using a cut-off score of ≥11 (34). Anxiety will be assessed using the Generalized Anxiety Disorder scale-7 (GAD-7) score (continuous) which is a reliable and validated measure for use during and after pregnancy. The GAD-7 consists of 7 items scored on a 4-point Likert scale which ask about common anxiety symptoms in the prior 2 weeks (range 0–21).

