Stress will be measured through two scales. First, perceived stress will be measured with the ten-item Perceived Stress Scale (PSS) (35). Scores range from 0–40 and will be categorized into three groups as low stress (0–13), moderate stress (14–26), and high stress (27–40). Second, parental stress will be measured using three modified subscales of The Parental Cognitions and Conduct Toward the Infant Scale (PACOTIS), including: parental self-efficacy (six items), perceived parental impact (five items), and parental overprotection (four items) (36). Items are scored from 0 to 10 with higher scores indicating higher levels of self-efficacy, parental impact, and overprotection. Mean scores for each subscale will be used for analysis. Ability to meet basic needs will be measured through three domains: financial, food, and housing insecurity. Financial insecurity will be measured using the 10-item Consumer Financial Protection Bureau Financial Wellbeing Scale (37). Continuous scores ranging from 0 to 20 will be categorized by quartiles for analysis (38). The validated, two question Hunger Vital Sign screener (39) will be used to measure households at risk of food insecurity, and housing insecurity will be assessed using up to 16 items on history of homelessness, history of eviction, and falling behind on rent and utilities. Engagement in health care will be captured using prenatal care attendance data from the birth certificates. Specifically, adequacy of prenatal care (APCNU) is assessed using the Kotelchuck index by creating a ratio of observed prenatal care visits to expected prenatal care visits, relative to the American College of Gynecology recommended standard of care, classified as inadequate, intermediate, adequate or adequate plus (40). Parent–child attachment will be assessed using the Maternal Postnatal Attachment measure, a validated continuous scale (41). The scale consists of 19 items which ask the birthing parent to reflect on their thoughts and feelings toward their baby (42).

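### The two item-missingness thresholds are not complements: scales with 20% to under 80% of items answered are neither imputed nor excluded, so incomplete scores may enter the EPDS and other outcomes

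*Protocol article*

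**What the plan says.** The section Preliminary and descriptive analyses of the protocol article gives two consecutive rules for partly answered scales. The first is the imputation rule: "Scale data where participants answered at least 80% of the items will be imputed using person-mean substitution". The second is the exclusion rule: where a participant "omits more than 80% of the items from a specific scale, responses from that scale will be excluded from analysis". The only other relevant sentence there is general: "Missing data will be assessed, and sensitivity analyses will be considered".

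The rules apply to the scale on which the study is powered. The Outcomes section says of the EPDS: "The scale consists of 10 items scored on a 4-point Likert scale", and then: "We will characterize this primary outcome using a continuous score". Probable depression is also derived from it, "using a cut-off score of ≥11". On anxiety the section says: "The GAD-7 consists of 7 items scored on a 4-point Likert scale". The PSS and the financial wellbeing scale have 10 items each and the attachment scale has 19. The three PACOTIS subscales have 6, 5 and 4 items and are analysed as means.

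**The concern.** Two rules of this kind should divide all respondents into those whose scale is completed and those whose scale is dropped. Here both sentences use 80%, but the first counts items answered and the second counts items omitted. The exclusion threshold looks like the complement of the imputation threshold with the wrong figure, 80% where 20% was meant.

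Followed literally, the text does not exclude a half-answered EPDS and prescribes no imputation for it. An analyst must then choose, possibly after seeing the data, whether to set the score to missing, prorate it or add up what is there. These choices give different data for the primary outcome. The last one pulls the score towards zero, which on the EPDS, GAD-7 and PSS looks like improvement.

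**Working it through.** **Which answered-item counts are covered.** For a scale of k items with a answered, the text imputes (or takes as complete) if a/k ≥ 0.80, and excludes if (k − a)/k > 0.80, that is, if a/k < 0.20. Everything with 0.20 ≤ a/k < 0.80 is uncovered. Exactly 20% answered belongs to the gap, because 80% omitted is not more than 80%.

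| Scale | Items | Complete or imputed | Excluded | Neither |
|---|---|---|---|---|
| EPDS, PSS, financial wellbeing | 10 | 8–10 | 0–1 | 2–7 |
| GAD-7 | 7 | 6–7 | 0–1 | 2–5 |
| Attachment | 19 | 16–19 | 0–3 | 4–15 |
| PACOTIS self-efficacy | 6 | 5–6 | 0–1 | 2–4 |
| PACOTIS impact | 5 | 4–5 | 0 | 1–3 |
| PACOTIS overprotection | 4 | 4 | 0 | 1–3 |

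On the EPDS, six of the eleven possible counts (0 to 10) have no rule. With an exclusion threshold of more than 20% omitted, the test becomes a/k < 0.80. This is the exact complement of the imputation rule, and the last column is empty for every scale.

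**The yardstick.** The section Power and sample size gives SD 6.24, groups of 164 and 117, two post-baseline observations, two-sided alpha 0.05, 80% power and a within-participant correlation ρ of 0.3 to 0.5. The detectable difference is

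(1.960 + 0.842) × 6.24 × √((1 + ρ)/2) × √(1/164 + 1/117).

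This gives 1.83, 1.77 and 1.71 for ρ = 0.5, 0.4 and 0.3 (stated: 1.8, 1.8, 1.7). With 123 and 88 participants and ρ = 0.5 it gives 2.11 (stated: 2.1). The plan's figures reproduce, and they do not depend on the item rule.

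**What a raw sum would do.** This step rests on two assumptions that the article does not state: that uncovered scores are summed as they stand, and that items are equal on average. The planning mean of 10.45 is then 1.045 per item.

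- 7 answered: 7 × 1.045 = 7.3, a shortfall of 3.1.
- 5 answered: 5 × 1.045 = 5.2, a shortfall of 5.2.
- 2 answered: 2 × 1.045 = 2.1, a shortfall of 8.4.

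Each shortfall exceeds 1.8 points. If EPDS items are scored 0 to 3 (assumed; the article says only that there are four response points), three or fewer answers total at most 9 and cannot reach the cut-off of 11.

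**Where this does not apply.** For a scale analysed as a mean, person-mean substitution changes nothing. If the a answered items have mean m, the completed mean is (a·m + (k − a)·m)/k = m. The PACOTIS subscales are therefore not pulled towards zero, although it remains unstated whether such records are kept.

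**The case against.** A reader might infer that the plan intends to sum partial items and that the treatment contrast on the primary outcome will be biased. The documents do not support this. The article never says that partial items are added up; it is silent on the middle band, and those scores could equally be set to missing or prorated.

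A bias in the contrast also needs more such records in one group than in the other, and no figure in the documents gives that. Purely as an illustration, suppose every such record is half complete and raw-summed, and one group has an excess at both follow-up visits. An excess of 1 percentage point shifts the contrast by 0.01 × 5.2 = 0.05 points, and an excess of 10 points by 0.52, which is 29% of 1.8. If the excess occurs at one visit only, the shift is about half of that. Ten points in the cash + care group would be about 16 additional half-empty questionnaires per visit (0.10 × 164).

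The documents point to few such records. Under Quantitative data collection, interviewers put every question to the participant by telephone, and REDCap checks are used against omissions. Under Community involvement in instrument development, the advisory board voted on measures, named topics it found unacceptable and pilots each survey. Data quality is also to be examined before modelling.

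All of this stands, and it limits the likely size and the severity. It does not supply a rule for the middle band. Nor is this a detail that a condensed article may leave to a fuller plan: the article states the exclusion threshold, and the stated figure does not fit the sentence before it. Prorating the middle band would not rescue the text, since it would allow an EPDS score built from two answers and make the 80% requirement pointless.

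**Conclusion.** The point holds as an inconsistency in a stated rule. Respondents who answer 20% to under 80% of a scale are neither imputed nor excluded, and this includes the EPDS. That follows from the text alone. Incomplete scores may enter the primary and other sum-score outcomes; that they will is not shown.

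The size is conditional. Under raw summing with items equal on average, a half-answered EPDS at the planning mean loses about 5.2 points, against a detectable difference of 1.8. How many records are affected is unknown and probably small, and a difference between groups is not documented. The model, the sample size and the power figures are unaffected. This is a minor correction, not a must-fix.

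**What to change.** Change the exclusion rule so that a participant who omits more than 20% of a scale's items (answers fewer than 80%) has that scale score set to missing. The two rules are then exact complements on every scale: a score is complete or person-mean imputed at 80% or more answered, and otherwise missing. For the EPDS and anxiety scores, the planned mixed effects model can still use that participant's other visits.

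The change is one number and one clause. Its cost is that a few more scale scores become missing. It should be made before the scores are computed, so that the treatment of partly answered scales is not chosen with the data in view.

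### The Aim 2 mixed model has time as its only fixed effect, so it cannot give the between-group difference it is said to estimate, and it does not fit single-value prenatal care adequacy

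*Protocol article*

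**What the plan says.** All of the following is in the protocol article.

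- **Aim 2, population.** The aim is framed as effects on parental stress, "ability to meet basic needs, engagement in healthcare and bandwidth for parenting among recipients of the cash + care". The quantitative part is meant to show whether cash + care "affects outcomes using two steps". The first step covers recipients only: "First, we will describe baseline demographic characteristics among those who receive cash + care".
- **Aim 2, model.** "We will use mixed effects regression models with a fixed effect for time (categorical) and random participant-level intercepts". The time points are the baseline, 6-month and 12-month surveys. The sensitivity analysis adds socioeconomic and pregnancy-related covariates and does not add group.
- **Aim 2, promised estimate.** Using those models, "we will estimate and report the average difference in outcome between groups over follow-up with 95% confidence intervals".
- **Aim 3, for comparison.** The depression model has fixed effects for time, "group, and the interaction between time and group and random participant-level intercepts". A nearly identical reporting sentence follows it.
- **Outcomes.** "Engagement in health care will be captured using prenatal care attendance data from the birth certificates", classified into four adequacy categories. Parent–child attachment "will be assessed using the Maternal Postnatal Attachment measure, a validated continuous scale". Perceived stress is grouped into three levels, financial wellbeing into quartiles, and food insecurity is a two-question risk screen.

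**The concern.** The model and the estimate are both stated, and they are incompatible. A model whose only fixed effect is time describes how the mean outcome moves across surveys. It says nothing about how the two lottery groups differ. The two recipients-only phrases suggest one analysis and the promise of a between-group difference suggests another, so the text does not fix which will be run.

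The choice matters because baseline is at 12–24 weeks of pregnancy and follow-up is at 6 and 12 months after birth. The article's Introduction itself says that financial insecurity often rises around childbirth, with household income falling by up to 10%. Stress and basic needs may therefore change over this period without any cash. A time effect in recipients alone would absorb that change, and could show an effect where there is none or hide a real one.

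A second mismatch concerns engagement in care, which Aim 2 lists among the outcomes followed over the three surveys. The Outcomes section derives it once, from the birth certificate.

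**Working it through.** **1. Parameters in each stated model.** Let *t* be baseline, 6 or 12 months, *g* = 1 for cash + care, and *b* a participant intercept.

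| | Fixed effects stated | Coefficients | Group difference at follow-up |
|---|---|---|---|
| Aim 2 | time | β0, β6, β12 | none available |
| Aim 3 | time, group, time × group | β0, β6, β12, γ, δ6, δ12 | γ + (δ6 + δ12)/2 |

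The promised Aim 2 estimate corresponds to the last cell of the Aim 3 row. Nothing in the Aim 2 row can produce it, whichever participants are included.

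**2. What the Aim 2 time coefficients would estimate.** Let τ be the change from pregnancy to postpartum common to everyone and θ the effect of cash. With complete data:

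- Recipients only: time effect = τ + θ. The care-only group is unused: 117/281 = 41.6%.
- Both groups pooled: time effect = τ + (164/281)θ = τ + 0.58θ. Everyone is used, but there is still no group coefficient.

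Neither isolates θ.

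**3. The plan's own power figure.** The article gives no power figure for Aim 2. The Power and sample size section covers Aim 3 (164 and 117 participants, SD 6.24, two postpartum observations, two-sided alpha 0.05, 80% power). With ρ the within-participant correlation:

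MDD = (1.960 + 0.842) × 6.24 × √((1 + ρ)/2) × √(1/164 + 1/117)

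- ρ = 0.5: 1.83 (stated 1.8)
- ρ = 0.4: 1.77 (stated 1.8)
- ρ = 0.3: 1.71 (stated 1.7)
- 123 and 88 after 25% dropout, ρ = 0.5: 2.11 (stated 2.1)

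These reproduce, and this point does not dispute them.

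**4. Illustration of the mixing.** The article gives no effect or trend for any Aim 2 outcome, so this borrows the depression-score inputs (SD 6.24, ρ = 0.5, 164 and 117, complete data). It assumes values of ±1.8 for τ and θ. The contrast is the mean of the 6- and 12-month values minus baseline, with 2,000 simulated trials per row.

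| Assumed θ | Assumed τ | Recipients only, time effect | Rejects | Group-by-time contrast | Rejects |
|---|---|---|---|---|---|
| 0 | −1.8 | −1.81 | 99% | −0.01 | 4.8% |
| −1.8 | 0 | −1.80 | 99% | −1.80 | 78% |
| −1.8 | +1.8 | −0.01 | 5% | −1.79 | 78% |

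An arithmetic check: the contrast has SD 6.24 × √(0.5 × 1.5) = 5.40. Its standard error is 5.40/√164 = 0.42 in recipients and 5.40 × √(1/164 + 1/117) = 0.65 between groups. So 1.8 is about 4.3 and 2.8 standard errors, in line with the simulated rates. The recipients-only analysis is right only when τ = 0.

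**5. Outcomes against the three-survey model.** Prenatal care adequacy is one ratio of observed to expected visits per pregnancy. With one value per person there is neither a time effect nor a within-person variance to model. Postnatal attachment asks about feelings toward the baby, so a pregnancy baseline is implausible. It could still be modelled on the 6- and 12-month values.

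**The case against.** The strongest reply is that the group terms were simply left out. Aim 2's reporting sentence nearly repeats Aim 3's, the design section describes two groups, and the descriptive analyses summarise baseline by intervention group. The recipients-only framing also fits the qualitative, how, half of Aim 2. This is plausible, and it limits what can be claimed:

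- A reader might infer that the comparison group is ignored and an uncontrolled before–after study is planned. The documents do not support that, because the same paragraph promises a between-group estimate.
- The 42% unused holds only under the recipients-only reading.
- The 99% and 5% rejection rates rest on assumed trends for an Aim 3 outcome. They show the mechanism and do not size the bias in any Aim 2 outcome.
- A reader might also infer that the parenting subscales have no pregnancy baseline. The article gives no schedule of measures by wave and calls the subscales modified, so that is not established.
- Aim 3's continuous-score model cannot simply be copied, since several Aim 2 outcomes are defined as categories.

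The central point survives. Even as an oversight, the stated model cannot give the stated estimate, and nothing elsewhere in the article supplies a group term for Aim 2. Nor is it a detail that an article leaves to a fuller document, because both the model and the estimate are given. The prenatal care mismatch is not answered either.

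**Conclusion.** The point holds in two parts. First, the Aim 2 model as stated contains no between-group parameter, so it cannot deliver the promised difference or show whether cash + care affects outcomes. This follows from the listed terms and needs no assumption. Second, prenatal care adequacy has one value per pregnancy and cannot be analysed with the three-survey model.

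Confounding with the change from pregnancy to postpartum, and the loss of 117 of 281 participants, depend on the recipients-only reading, which the text allows but does not establish. The size of any resulting bias is unknown, because the article gives no expected trend for the Aim 2 outcomes.

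The defect affects the whether question of one of the three named aims. The lottery, data collection, sample size and powered depression analysis are untouched.

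**What to change.** Reword the Aim 2 analysis paragraph as follows.

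- State that Aim 2 uses both lottery groups, with fixed effects for time, group and time × group and a participant random intercept, as in Aim 3.
- Choose the link for each outcome as the Outcomes section defines it, for example ordinal or logistic for categorised stress, financial wellbeing and food insecurity. Report the between-group difference over the 6- and 12-month follow-up on the matching scale.
- Analyse prenatal care adequacy with one between-group ordinal or logistic regression.
- For any outcome measured only after birth, such as postnatal attachment, compare the groups on the postpartum waves only.
- Label any change over time within recipients as descriptive and not as an effect of guaranteed income.

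The cost is a text change, best made before outcome data are analysed. Both groups complete the baseline survey, and the power section already assumes postpartum observations from both, so no further data collection is needed.

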#### Quantitative data collection

Quantitative data collection takes place at enrollment (12–24 weeks gestation) and at 6 and 12 months postpartum (Figure 3). Participants in both groups (i.e., cash + care and care only) complete the baseline survey prior to receiving the cash disbursement, financial counseling, or care services. Survey data is collected through REDCap, a secure, web-based application that complies with HIPAA regulations. All data collection procedures follow approaches used in other local studies. Each survey is administered via an interviewer over the phone. Each question is read to the participant; responses are recorded on a tablet with a secure internet connection. All data management standards reflect the goal of reproducible research. To reduce data entry errors and omissions, we take advantage of REDCap’s built-in quality control functions. Data integrity is aided by the system’s automated logging of all input and edits. After each survey is complete, CRs send the participant a gift card (electronically or by text) and a community resource guide. Participants receive $50 for completion of the baseline survey, and the amount is increased by $25 for each subsequent survey.

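### The Aim 2 model has time as its only fixed effect, so it cannot give the between-group difference that the same paragraph promises; the recipients-only wording also conflicts with that estimand

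*Protocol article*

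**What the plan says.** All of this is in the protocol article, Part 4.

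- **Population.** Under Quantitative data analysis, Aim 2, the objective covers "engagement in healthcare and bandwidth for parenting among recipients of the cash + care". The first step is: "First, we will describe baseline demographic characteristics among those who receive cash + care".
- **Contrast.** The second step looks at differences in parental stress, basic needs, engagement in care and "bandwidth for parenting over follow-up (baseline, 6 months postpartum, and 12 months postpartum surveys"). It names no population and no comparator.
- **Model.** "We will use mixed effects regression models with a fixed effect for time (categorical) and random participant-level intercepts". Sensitivity to SES and pregnancy-related covariates is to be examined.
- **Reported result.** "Using these models, we will estimate and report the average difference in outcome between groups over follow-up with 95% confidence intervals".
- **Aim 3, by comparison.** The depression model has fixed effects for time, "group, and the interaction between time and group and random participant-level intercepts".
- **Data.** Under Quantitative data collection: "Participants in both groups (i.e., cash + care and care only) complete the baseline survey". The survey schedule is enrollment (12 to 24 weeks of gestation) and 6 and 12 months postpartum.

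**The concern.** The stated model and the stated result do not fit together. Aim 2 carries the question of whether guaranteed income changes stress and the ability to meet basic needs. An analyst who follows the model sentence gets changes over time and no comparison. An analyst who follows the reporting sentence must add terms that the text does not list. The choice between a one-group and a two-group analysis is thus left open until the data are in hand.

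The recipients-only wording adds a second risk. Baseline falls in mid-pregnancy and follow-up in the first postpartum year. The Introduction says that household income can drop by up to 10% in the months around pregnancy, so some movement in these outcomes without any cash is plausible. A before-after contrast in recipients could credit that movement to cash. It could equally hide a real benefit, if hardship rises in everyone and cash only softens the rise.

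**Working it through.** **1. The plan's own figures.** The article gives no power figure for Aim 2. Its Aim 3 figures reproduce, which confirms the inputs used below (Power and sample size: 164 vs 117; 123 vs 88 after 25% dropout; SD 6.24; two-sided alpha 0.05; correlation r from 0.3 to 0.5).

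Detectable difference = (1.960 + 0.842) × 6.24 × sqrt((1+r)/2) × sqrt(1/164 + 1/117)

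- r = 0.5, 0.4, 0.3: 1.83, 1.77, 1.71 (stated 1.8, 1.8, 1.7)
- 123 vs 88, r = 0.5: 2.11 (stated 2.1)

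**2. What the stated model can estimate.** Write the outcome as y = intercept + time effect + random intercept + error. No coefficient refers to group. Let T be the change that would occur without cash and C the effect of cash.

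- Recipients only: the time coefficient estimates T + C. The two cannot be separated.
- Both arms, complete data: the time coefficient estimates T + (164/281) × C = T + 0.58 C. This is still not a difference between groups.

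Baseline covariates added as main effects shift each person's level. They do not remove a change over time that is common to everyone.

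**3. Size under the recipients-only reading.** Contrast: mean of 6 and 12 months minus baseline, in SD units.

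SE = sqrt(v/n), with v = (1+r)/2 + 1 − 2r, so v = 1.05 at r = 0.3 and 0.75 at r = 0.5.

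Probability of a significant result = Φ(d/SE − 1.96) + Φ(−d/SE − 1.96), where d is the natural shift and C = 0. The values of d are assumptions.

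| n | r | SE | d = 0.1 | d = 0.2 | d = 0.3 |
|---|---|---|---|---|---|
| 164 | 0.3 | 0.0800 | 0.24 | 0.71 | 0.96 |
| 164 | 0.5 | 0.0676 | 0.32 | 0.84 | 0.99 |
| 123 | 0.3 | 0.0924 | 0.19 | 0.58 | 0.90 |
| 123 | 0.5 | 0.0781 | 0.25 | 0.73 | 0.97 |

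**4. Simulation check at r = 0.5.**

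- 123 vs 88, common shift 0.2 SD, no cash effect (5,000 runs): the one-group contrast rejects in 73.4%, the two-group contrast in 4.5%.
- 164 vs 117, SD 6.24, no cash effect (2,000 runs per scenario): a common change of 1 point in either direction gives about 66% rejection for the one-group contrast. The two-group contrast rejects in 4.0 to 6.0% across common changes from −2 to +2 points.
- Masking: with a true effect of −1.8 and a common rise of +1.8, the one-group contrast averages 0.0 (5% rejection). The two-group contrast averages −1.8 (79% rejection).

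**5. Precision of the two-group change contrast.** Detectable difference = 2.80 × sqrt(v) × sqrt(1/n1 + 1/n2).

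- 164 vs 117 (last factor 0.1210): 0.29 SD at r = 0.5, 0.35 SD at r = 0.3
- 123 vs 88 (last factor 0.1396): 0.34 SD at r = 0.5, 0.40 SD at r = 0.3

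**The case against.** The best defence is that a two-group analysis was intended and the group terms were dropped in drafting. The sentence on what will be reported speaks of groups and nearly repeats the Aim 3 sentence. The section on preliminary and descriptive analyses summarises baseline by intervention group and allows plots of repeated measures by assigned treatment. The study design sets up a comparison group. The model sentence itself names no population: the recipients-only wording stands in the objective and in the descriptive first step.

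Most of this stands. A reader might infer that the article commits Aim 2 to a before-after analysis and that natural perinatal change will be reported as an effect of cash. The documents do not support that as a certainty; it follows only if the recipients-only wording governs the model. The defence does not rescue the model sentence, however. The reported difference is to come from the models just described, and those have no group term under either reading. Nor is this detail left to an analysis plan, since the article states the model terms for both aims and states them differently.

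Three further limits hold. The Introduction's income figure makes a shift plausible but does not show how stress, food or housing scores move. Calculations in SD units are illustrative, because the article cuts perceived stress into three groups and financial wellbeing into quartiles and measures food insecurity with a two-question screener. Covariates that predict dropout can matter when the sample changes between waves, so the sensitivity analysis is not useless; it just does not deal with a common trend.

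**Conclusion.** The Aim 2 specification is wrong as written: the stated model cannot produce the stated estimate. This needs no assumption. The population wording also conflicts with the between-group estimand and has to be settled.

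The bias is conditional. It arises only if recipients alone are analysed, and its size rests on a natural shift that the article does not give, on approximate normality and on complete data. The rejection rates in the table show that even a modest common change would often be declared significant when cash does nothing.

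The primary depression analysis in Aim 3 has the group and interaction terms and is not touched.

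**What to change.** In Quantitative data analysis, Aim 2:

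- State that the quantitative analysis of whether cash has an effect uses both surveyed groups, and remove the restriction to recipients from that part.
- For outcomes measured at baseline, 6 and 12 months (perceived stress; financial, food and housing insecurity), use the Aim 3 terms: time, group and time-by-group, with a link suited to categorical outcomes. Report the cash + care versus care-only contrast over 6 and 12 months.
- For parent-infant measures, which have no meaningful pregnancy baseline, compare the groups at the postpartum waves. For prenatal care adequacy, taken once from the birth record, make a single between-group comparison. The Aim 3 model with baseline cannot be fitted to these outcomes, so it should not be copied across the whole aim.
- Keep the recipients' trajectories as description.

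The cost is wording only, because the care-only group is already surveyed. The price in precision is wider intervals than for a one-group change: a detectable difference of about 0.29 to 0.35 SD at 164 vs 117, and about 0.34 to 0.40 SD after 25% dropout, for correlations from 0.5 down to 0.3.
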